**Figure 5. fig5-20552076241311731:**
[figure not shown]
Overview of the within-person-encouragement-design specifications.

### Outcome measures

Primary outcomes will be assessed at a momentary level, with (momentary assessments conducted eight times per day during the nonintervention phase and eight times per day during the intervention phase:
The score of a single-item to measure the direct loneliness^
68
^ on a Likert scale ranging from 1 to 7 and the three-item ULS-3 to measure the indirect loneliness in English^
69
^ and the respective validated German version^
70
^ on a VAS with the range 0 to 100.The score of a single-item to measure direct craving^
71
^ using a Likert scale ranging from 1 to 7 and the five-item PACS to measure the indirect craving in English^
72
^ and the respective validated German version^
73
^ on a VAS with the range 0 to 100.Secondary outcomes will be assessed at a momentary level, with momentary assessments conducted eight times per day during the nonintervention phase and eight times per day during the intervention phase:
The score of a 6-item Multidimensional Mood Questionnaire measured on a Likert scale ranging from 1 to 6^
74
^The number and sort of standard drinks, German version^
43
^The score of a modified version of the five-item Drug Effects Questionnaire-5 to measure subjective response to alcohol in English^
75
^ and in German^76,77^ using the VAS ranging from 0 to 100The score of two modified single-items to assess control over drinking habits and feelings of loneliness^
78
^ measured on a VAS ranging from 0 to 100The score of a two-item scale to assess event appraisal^
79
^ using a VAS which ranges from 0 to 100The score of a three-item scale to measure momentary social contacts.^80,81^ This assessment includes the duration of social contacts in hours and minutes, as well as the quality of these contacts, rated on a VAS from 0 to 100Movement Acceleration Intensity (MAI) steps and Euclidean Norm Minus One (ENMO)^
82
^ assessed automatically via a *movisens* Move4 wrist-sensor.^
83
^Secondary outcomes measured on a daily basis (evening assessment conducted once per day):
The score of a modified four-item scale to measure motivation for alcohol consumption (social, coping, enhancement, and conformity)^43,84^ on a Likert scale from 1 to 5The score from three items inquiring about drug usage other than alcohol, including usage and, if applicable, dosage of other drugs as well as cigarettes. The specific list includes: substances for sniffing (e.g. glue), tranquilizers or sedatives, stimulants (e.g. amphetamines, methamphetamines), hallucinogens (e.g. drug mushrooms, crack cocaine, cocaine), relevin, heroin, narcotics, ecstasy, ketamine or phencyclidine, GB or liquid ecstasy, anabolic steroids. This list is adapted from the National Survey on Drug Use And Health by the U.S. Department of Health and Human Services, Substance Abuse and Mental Health Services Administration^
85
^The score of a modified two-item Patient Health Questionnaire-2^
86
^ on a Likert scale from 1 to 4The score of a modified two-item Generalized Anxiety Disorder Scale-2^
87
^ on a Likert scale from 1 to 4The score on a single item measuring the stressfulness of the day on a VAS ranging from 0 to 100 modified form Preston and coworkers^
88
^The score of two 3-item Intention to Cope Questionnaires, modified to address loneliness^
89
^ and craving^
90
^ on a VAS from 0 to 100The score of a 4-item Brief Impulsivity Scale^
91
^ on a Likert scale ranging from 1 to 5The score of a single item considering limiting the alcohol consumption on the following day using a VAS from 0 to 100 modified from Howard and coworkers^
92
^The score of a single item derived from the Reward Probability Index^
93
^ on a Likert scale ranging from 1 to 4The score of a gamified stop-signal-task to measure response inhibition^
50
^The score of a six-item scale to measure reappraisal using a VAS which ranges from 0 to 100^
94
^To gain a deeper understanding of the interventions’ effects, we will monitor participants’ use of reappraisal during the physical activity intervention and vice versa. After each encouragement condition, we will calculate both the MAI and ENMO scores and assess reappraisal using the abovementioned six-item scale.^
94
^

Upon the participants’ return with the smartphone and wearable devices, we will conduct a qualitative semistructured interview, which will be audiorecorded and later transcribed. The following questions will be asked:
How feasible did you find the cognitive reappraisal, physical activity, gamified working memory task?How engaged were you in the cognitive reappraisal, physical activity, gamified working memory task?How acceptable did you find cognitive reappraisal, physical activity, gamified working memory task?What did you find most frustrating or annoying about the app?How could the study be improved?What did you find most frustrating or annoying about the study in general?Did your participation in the study (cognitive reappraisal, physical activity, gamified working memory task) help reduce your alcohol consumption? If so, how?Did your participation in the study help reduce your feelings of loneliness? If so, how?Did your participation in the study help reduce your craving for alcohol? If so, how?How honestly did you complete the queries and interventions (cognitive reappraisal, physical activity, gamified working memory task)?

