^ Recent studies argue for craving to be a promising causal marker with prognostic value and high potential as a treatment target for interventions triggered by ecological momentary assessment (EMA).^
10
^

The EMA methodology (e.g. smartphone-based electronic diaries and wearables) enables to investigate intra- and interindividual effects as well as reciprocal relationships.^11,12^ EMA involves repeatedly sampling of individuals’ behaviors and experiences in real-time within their natural environments. This method minimizes recall bias and enhances ecological validity, while approximating temporal dynamics (e.g. Granger causality).^
13
^ However, EMA can also impose a burden on participants, requiring them to respond to repeated questionnaires throughout the day, which may disrupt ongoing activities and cause distress.^
14
^ We can apply EMA to gather intensive longitudinal data (ILD) on determinants and consequences of drug intake.^
15
^ On the one hand, ILD is more ecologically valid, as it directly measures the subjects’ experience in their current environment; on the other hand, it allows to approximate temporal associations. However, causal inferences can only be established if: (1) variables of interest are correlated with each other, (2) a temporal order is given, (3) hidden third variables are controlled or explained; and (4) the direction of the effect is indispensable (e.g. heightened levels of craving usually correspond to increased alcohol consumption).^
16
^ Accordingly, experimental designs enable to test for causality through experimental manipulation under laboratory conditions and control of potential hidden influences.^
17
^

To approximate causality and test temporal directionality underlying drug intake in everyday life, we need to combine the advantages of laboratory and ambulatory approaches. This combination allows us to achieve both ecological validity and approximate causal temporal inferences (i.e. an ecological approach to intervention). EMA enables the collection of time series data, which can be used to approximate the temporal necessity of causality, known as Granger causality (i.e. where the cause precedes the effect).^
18
^

Just-In-Time-Adaptive-Interventions (JITAIs)^
19
^ are recognized as a first key step toward approximating causality within subjects in everyday life.^
20

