**Figure 4. fig4-20552076241311731:**
[figure not shown]
Illustrative screenshots from the comic elucidating cognitive reappraisal. This comic was created by us using the AI image generator Midjourney.

The JITAI will take approximately 6 min. It will begin by prompting participants to describe the situations in which they encountered feelings of loneliness or cravings. Subsequently, they will be asked to articulate the thought that most triggers their loneliness or craving. Finally, participants will be tasked with documenting how they challenge this thought, employing four reappraisal strategies.^
60
^ (1) Considering disadvantages: What are the disadvantages of thinking like this if I want to reach my goals to drink less or not to feel lonely. (2) Checking reality: Have I had any experiences to show that this mental statement is not always true? (3) Use other people as a reference point: What would someone who knows to handle this situation well say if they knew I was trying to reduce my drinking/not to feel lonely? (4) Imagine giving advice: What advice could you give to a close person in a similar situation? After each reappraisal, participants will be asked to rate their conviction regarding the thought related to loneliness or craving on a horizontal Visual Analog Scale (VAS)^61,62^ ranging from 0 (“not convinced at all”) to 10 (“strongly convinced”). In addition, they will be prompted to assess the difficulty of reappraising the specific situation using a horizontal VAS ranging from 0 (“strongly disagree”) to 10 (“strongly agree”).

*Intervention 2 (physical activity)*. The physical activity intervention will be designed to increase participants’ step count within a set timeframe. Previous studies have been found that moderate-intensity exercise sessions lasting 5 to 15 min can significantly reduce alcohol cravings.^36,63–65^ Accordingly, our physical activity intervention encourages participants to take a brisk 6-min walk (or engage in indoor walking). During this activity, the number of steps per minute is tracked using a *movisens* Move4 wrist-sensor, providing participants with real-time feedback on their walking pace. Control measures involve automatically assessing the number of steps taken during exercise using the *movisens* Move4 activity sensor.

*Active control (a gamified working memory task)*. The working memory is facilitated by the Great Brain Experiment app,^
66
^ which has been tested and validated in German.^
50

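### The three exit-interview questions on effects ask only about reduction, which steers the interview's effect themes toward benefit

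*Protocol article*

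**What the plan says.** The Outcome measures section ends with the exit interview: "we will conduct a qualitative semistructured interview, which will be audiorecorded and later transcribed. The following questions will be asked". Ten questions follow. Three ask about effects of taking part:

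- Alcohol consumption: the question names the three tasks and asks whether participation did "help reduce your alcohol consumption? If so, how".
- Loneliness: "Did your participation in the study help reduce your feelings of loneliness? If so, how".
- Craving: "Did your participation in the study help reduce your craving for alcohol? If so, how".

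The other seven cover feasibility, engagement, acceptability, annoyances with the app, suggestions for improvement, annoyances with the study ("What did you find most frustrating or annoying about the study in general") and honesty of completion. The Data analysis section assigns the interview material to thematic analysis, with codes generated from the transcripts and grouped into themes.

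Two other places bear on the point. The Introduction says that repeated momentary questionnaires burden participants, "which may disrupt ongoing activities and cause distress". In the description of Intervention 1 (Design and procedure), participants first describe the situation in which they felt lonely or craved alcohol, and then "they will be asked to articulate the thought that most triggers their loneliness or craving".

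**The concern.** A question that names one direction and follows up only on agreement is a leading question. A participant whose craving rose after a prompt can truthfully answer no, but so can a participant who noticed nothing. The listed wording does not separate the two, and it asks neither of them for detail. Thematic analysis builds its themes from what is said, so benefit will come with mechanisms and examples, while absence of effect and worsening will come mostly as a bare no.

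This matters somewhat more here than in most app studies. Encouragement is triggered when loneliness or craving is already rated high, and the reappraisal task directs attention to the thought that provokes that state. The Introduction describes craving as a major predictor of relapse, and the Discussion suggests the platform for people awaiting formal treatment. What participants saw as unhelpful or provoking is information the authors would want, and it is hard to recover once the interviews are over.

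**Working it through.** No sample-size, power or error-rate figure is involved. The check is a count of the listed questions by direction, followed by a comparison with the other participant-reported measures.

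**Step 1. Count the ten questions** (Outcome measures, interview list).

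| Content | Number |
|---|---|
| Feasibility, engagement, acceptability of the tasks | 3 |
| Frustrations or annoyances (app; study in general) | 2 |
| How the study could be improved | 1 |
| Effect on drinking, loneliness, craving | 3 |
| Honesty of completion | 1 |
| Total | 3 + 2 + 1 + 3 + 1 = 10 |

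Of the 3 effect questions, 3 are worded as reduction with a follow-up conditional on yes. Of the 10 questions, 0 ask about no change or an increase.

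**Step 2. Do the other questions cover worsening?** The two on frustrations and the one on improvement invite negative comment, and a participant could use them to report distress. They ask about the experience of the app and the study, not about a change in drinking, loneliness or craving. Worsening would have to be volunteered there or drawn out by the interviewer.

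**Step 3. What else do participants report?** Primary loneliness is scored by a single item "on a Likert scale ranging from 1 to 7 and the three-item ULS-3 to measure the indirect loneliness in English", the latter on a 0 to 100 visual analogue scale. Craving is scored in the same two ways. Mood and number of standard drinks are also momentary measures, listed at eight times per day. Short depression, anxiety and day-stress items are added each evening. All of these can rise or fall. At the end of the 21 intervention days a reactance scale records negative reaction to the interventions.

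**Step 4. Which analyses use which data?** The Data analysis section estimates the intervention effects on loneliness and craving by instrumental variables in two-level models, and tests changes in drinking and pre–post differences by multilevel models. Both use the momentary data. The interview feeds only the thematic analysis. The leading wording can therefore affect the interview's effect themes and nothing else that is planned.

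**Step 5. Does the interview add anything?** Yes, in one respect. Momentary questionnaires are sent eight times per day in the baseline week, the intervention weeks and the follow-up week (Design and procedure). A shift caused by the questioning itself, and shared by all these periods, would largely cancel from the encouraged versus unencouraged contrast and from the pre–post contrast. The participant's own account is one of the few places where it could surface, so the direction of the question is worth getting right.

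**The case against.** The strongest reply is that this is a small wording matter in a supplementary component. Both hypotheses, the primary and secondary outcomes and the effect models rest on momentary data. Encouragement is randomised, with one of three daily situations left unencouraged, and the resulting estimate can show harm as readily as benefit. It is better evidence on whether prompts raise craving than recollection at study end. The interview is semistructured, participants can answer no, and an article need not print the interviewer's probes. All of this stands, and it limits the point to the qualitative part. It does not remove the point, because the criticism is of wording that the article prints, not of something it leaves out.

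A reader might go further and infer that everything participants report about effects can only favour the interventions. The documents do not support that: the momentary and evening scores run in both directions, and the reactance scale collects unfavourable reactions. Nor do they support saying that distress from repeated questioning would go unseen, since mood, anxiety and stress are measured and the question on annoyances with the study invites that complaint.

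A reader might also try to size the bias by exposure: up to 2 encouraged prompts × 21 days = 42, or 8 questionnaires × 35 days = 280. These are counts of contact, not of bias. The 42 is a maximum spread over reappraisal, walking and the memory task, and only reappraisal asks for the triggering thought. The 280 includes 14 days (7 + 7) without any intervention.

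**Conclusion.** The point holds for the exit interview alone. All three effect questions are leading (3 of 3), and no listed question asks about no change or worsening (0 of 10). The effect themes of the thematic analysis will tend toward benefit, by an amount the documents do not allow one to estimate. The primary and secondary quantitative estimates are not affected.

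This assumes that the interview follows the listed wording, as the article says it will, and that no neutral probe in an interview guide not shown already covers increases. If such a probe exists and is used consistently, little remains. The point is minor, and worth acting on because the remedy costs little.

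**What to change.** Reword the three effect questions neutrally, for example: *Did taking part change your alcohol consumption (then: your loneliness; your craving): decreased, no change or increased? How, and which task or prompt played a part?* Asking about the task also makes the loneliness and craving questions match the alcohol question, which already names the tasks. Add one open question, for example: *Did any task or questionnaire make you feel worse or want to drink?*

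A prespecified worsening theme with reported counts is not needed. The article generates its codes from the data, and a different qualitative approach is a matter of preference.

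The cost is a few more minutes per interview and a notification to the ethics committees. Recruitment began in June 2024, so some interviews may already have been held. Those that used the current wording should be identified separately in the report. Randomisation, outcomes, sample size and the statistical models stay as they are.

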### Data analysis

We will analyze the resulting ILD using structural equation and multilevel modeling (MLM) with *R and Mplus*. The procedure including data preprocessing, analysis, and modeling is more detailed below. To preprocess EMA data, we will follow established state-of-the-art procedures detailed in methods guidelines.^
12
^ Physical activity data will be preprocessed by computing established metrics such as MAI and merged with the e-diary data (software Data Merger, *movisens* GmbH, Karlsruhe).

To assess the effectiveness of our interventions (i.e. cognitive reappraisal and physical activity) in reducing loneliness and cravings, we will employ instrumental variable estimation and build two-level structural equation models for path analyses,^
21
^ illustrated in Figure 5. On the first level (Level 1), we will estimate repeated measurements within subjects. In the path analyses, we will model (i) direct effects of the instrumental variable (encouragement for intervention) on the treatment (cognitive reappraisal and physical activity); (ii) the treatment effect on the target/outcome variables (i.e. loneliness or/and alcohol craving); and (iii) the residual (co-)variances (σ^2^_T_, σ^2^_0_, ψ_T0_) of the treatment (е_T_) and outcome (е_O_) on the within-subject level. On the second level (Level 2), we will estimate between subject differences in means, intercepts, and regression coefficients as random effects. Beyond two-level structural equation models, we will use established MLM procedures to test for within-subject changes in alcohol consumption and for pre–post differences in both mean levels of alcohol-use triggers (i.e. loneliness or/and alcohol craving).

For nonsystematic missing data,^
47
^ we will impute the missing values using the standard procedure.^
95
^ Specifically, we will employ the R package Multiple Imputation via Chained Equations to handle missing data through an iterative predictive modeling process.^
14
^ For the MLM and multilevel structural equation modeling analysis, we will employ the default FIML/MCM procedure in *Mplus*. In addition, we plan to explore the effects of reappraisal and physical activity in comparison to a no-intervention condition within a subsample of participants. The qualitative data will be analyzed using thematic analysis with the software MAXQDA. Our general approach involves identifying, analyzing, and reporting key themes. Specifically, we will read and reread the data to gain a deep understanding, generate initial codes, and group these codes into potential themes. We will then refine and review the themes to ensure they accurately reflect the data. Each theme will be clearly defined and named, and we will integrate the themes with relevant data extracts for reporting purposes.

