^ The task is gamified to enhance participant engagement and is designed based on a widely used delay-match-to-sample task.^
67
^ For more detailed description of the task, see Brown et al.^
66
^

Randomized encouragement to engage in one of the abovementioned interventions is triggered through *movisensXS*, particularly in contexts where participants’ ratings indicate a high momentary level in at least one of the following target situations: i) high loneliness only, ii) high alcohol craving only, and iii) both high loneliness and craving alcohol. We will limit the number of triggers for interventions to a maximum of 3 per day. While two-third of these situations (*n* = 2), encouragement to engage in an intervention will be provided, the remaining situation (*n* = 1) serve as control condition without encouragement. Loneliness and alcohol craving are detected in real-time via analyses of the participants’ e-diary ratings, and physical activity is monitored via a sensor attached to the participants’ hip (*movisens* move-4), which is connected to the smartphone via Bluetooth low energy for data transfer and real-time analyses. To increase compliance, we will implement a “buffer time” of up to 60 min (see Figure 5).

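### The within-person path model names no covariate for the ratings that fire each trigger; adding them would gain precision, and a fixed daily 2:1 split, if that is meant, adds a same-day history imbalance

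*Protocol article*

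**What the plan says.** In the protocol article, Data analysis, Level 1 of the two-level structural equation model has three parts: "direct effects of the instrumental variable (encouragement for intervention) on the treatment (cognitive reappraisal and physical activity"), then "the treatment effect on the target/outcome variables (i.e. loneliness or/and alcohol craving"), then the residual variances and covariance of treatment and outcome. At Level 2, "we will estimate between subject differences in means, intercepts, and regression coefficients as random effects". No variable measured at the trigger is named.

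Design and procedure describes how triggers arise. "Loneliness and alcohol craving are detected in real-time via analyses of the participants’ e-diary ratings", and a trigger needs one of three situations: "i) high loneliness only, ii) high alcohol craving only, and iii) both high loneliness and craving alcohol". On number and allocation: "We will limit the number of triggers for interventions to a maximum of 3 per day", and "While two-third of these situations (*n* = 2), encouragement to engage in an intervention will be provided", with one situation left unencouraged. The article does not say how the order is drawn or what happens on days with fewer than three triggers. H1a (loneliness) and H1b (craving) are not tied to which state was high.

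**The concern.** Three kinds of information exist at each trigger before encouragement is assigned: the two ratings, which of them was high, and how many encouragements the person has already had that day.

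- **Ratings.** A baseline taken shortly before randomisation usually predicts the later rating. Left out, the variance it would explain stays in the Level 1 residual. Person-level random effects cannot absorb it, because it varies within person.
- **Trigger type.** Loneliness after a craving-only trigger was, by definition, not high. If the interventions act mainly on the raised state, an average over all triggers is smaller than the effect where the state was raised.
- **History.** If each day has a fixed two-to-one split, earlier assignments predict the current one. If effects also persist within the day, encouragement is then linked to the outcome by a route other than the current treatment, which an instrumental-variable analysis assumes away.

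**Working it through.** **Inputs from the protocol article.** 180 recruited, 20% dropout, 21 intervention days, 3 (non)encouragements per day, 70% compliance (Sample size and power considerations); at most 3 triggers per day, 2 encouraged and 1 not (Design and procedure). **Assumed, because the article gives no values:** within-person correlation r between triggering and later rating; carry-over fraction c; share p of triggers at which a given state is high.

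**1. The plan's own figure.** 180 × 0.8 = 144; 144 × 21 × 3 × 0.7 = 6350.4, which reproduces the stated 6350.

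**2. Value of the triggering rating.** Adjustment multiplies the residual variance by 1 − r², so the standard error (SE) by √(1 − r²) and the effective number of points by 1/(1 − r²).

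| r | SE factor | 1/(1 − r²) | 6350 points act like |
|---|---|---|---|
| 0.3 | 0.95 | 1.10 | 6978 |
| 0.5 | 0.87 | 1.33 | 8467 |

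Only high ratings fire a trigger, which restricts their range and makes the lower end more plausible.

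**3. Pooling over trigger types.** If the effect on a state exists only where that state is high, the pooled effect is p times that effect. With three equally common types p = 2/3, and a simulated true effect of −0.20 came out as −0.131. Restricting to relevant triggers keeps a share p of the points but the whole effect, so the information ratio is p/p² = 1/p: 1.5 at p = 2/3, and 2.0 to 1.25 for p = 0.5 to 0.8.

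**4. History under a fixed quota.** With E for encouraged and N for not, the three equally likely orders on a full day are EEN, ENE and NEE.

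- Earlier encouragements at the N occasion: 2, 1, 0; mean 1.0.
- Earlier encouragements at the two E occasions: 0 and 1 in every order; mean 0.5.

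If each earlier treatment carries over a fraction c of the effect, the estimate keeps 1 − (1.0 − 0.5)c = 1 − 0.5c: 95% at c = 0.1, 87.5% at 0.25 and 75% at 0.5. When only the first two triggers occur, the difference is 0.25 and the estimate keeps 1 − 0.25c. In simulation with a true effect of −0.20 and c = 0.5, the quota gave about −0.145 to −0.148; independent draws with probability 2/3 gave −0.199.

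**5. What adjusting for history costs.** Over the nine occasions, the variance of encouragement is 2/9, the variance of the count of earlier encouragements is 4/9 and their covariance is −1/9.

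- **Count alone.** R² = (1/81)/(2/9 × 4/9) = 1/8, so 87.5% of the instrument variance remains. Position is uncorrelated with encouragement but has covariance 4/9 with the count. Regressing position on encouragement (a) and count (b), with the equations multiplied by 9, gives 2a − b = 0 and −a + 4b = 4, so a = 4/7. A drift of d per trigger position would therefore bias the encouragement coefficient by 4d/7, a bias the unadjusted model does not have.
- **Count and position together.** 62.5% of the instrument variance remains with a linear count and 58.3% in a saturated form, so the SE rises by a factor of 1.26 to 1.31. With the triggering rating added (linear count), the SE factor is 1.21 at r = 0.3 and 1.10 at r = 0.5, still a net loss.

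**The case against.** The strongest reply is that this reads a condensed article's silence as a decision. The model is said to be illustrated in Figure 5, which is not shown, and a statistical analysis plan may list covariates. That stands in part: nothing excludes covariates, and the point is an available gain, not an error. But the section sets out the Level 1 components one by one, and the ratings are collected in any case, so naming them is a concrete improvement.

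A reader might go further and infer three things that the documents do not support.

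- **That the planned estimate is invalid without the covariates.** It is not: encouragement is randomised, and omitting a baseline does not bias the estimate.
- **That pooling trigger types is wrong and the restricted analysis should be primary.** H1a and H1b are not limited by trigger type, so the average over all triggers is a legitimate target. A state that is not high is not necessarily at its floor, on scales of 1 to 7 and 0 to 100 and in people selected for high trait loneliness and craving. A main effect for trigger type would not undo any dilution either.
- **That omitting earlier encouragements loses precision.** Under a quota the reverse holds: adjusting for them uses up instrument variance. The reason to consider them is bias.

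The carry-over bias is also conditional. It needs a fixed quota, random order and persistence within the day. The n = 2 and n = 1 wording favours a quota but does not settle it, three triggers is a maximum, and earlier encouragements to the working memory task may carry over little.

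**Conclusion.** The point holds as a recommendation to improve the analysis. The within-person model as written leaves unused a baseline collected before each randomisation; using it is worth about 10% to 33% more data points at an assumed r of 0.3 to 0.5. The state-specific effect merits a supporting analysis, because the pooled average would be smaller if effects are confined to the raised state; how much smaller rests on assumed values.

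The history imbalance of 1.0 against 0.5 is exact for a fixed daily quota in random order on three-trigger days. It becomes bias only with same-day carry-over, leaving 95% to 75% of the effect for c = 0.1 to 0.5, with less shrinkage on days with fewer triggers. The article does not establish the quota, and gives no value for r, c or p.

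**What to change.** 1. Add the triggering loneliness and craving ratings (person-mean centred) and trigger type (i, ii, iii) as covariates in both Level 1 equations. Cost: analysis wording and a few parameters; no new data.
2. Keep the pooled estimate for H1a and H1b. Report as supporting analyses the effect on loneliness at triggers i and iii and on craving at triggers ii and iii.
3. State how encouragement is drawn, including on days with fewer than three triggers. Where still feasible, draw it independently with probability 2/3 at each trigger. This removes the imbalance at source; the cost is a daily ratio that varies.
4. If a fixed quota stays, report a sensitivity analysis adjusting for trigger position and number of earlier encouragements together, noting that it leaves only about 60% of the instrument variance. Do not adjust for the count alone, which introduces bias if ratings drift over the day.
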